## Abstract

Virtual reality (VR) is a valuable tool for the treatment and prevention of psychiatric disorders and dysfunctional behaviors. Although VR software is mainly developed following a disorder-specific approach, this randomized controlled trial (RCT) will test the efficacy of a new transdiagnostic VR application (H.O.M.E. VR-based psychological intervention) in improving dysfunctional behaviors, three transdiagnostic factors concurrently (emotion regulation, experiential avoidance, and psychological flexibility), and stress. Three groups screened as at-risk for nicotine dependence, alcohol abuse, and eating disorders will be assigned to the H.O.M.E. VR intervention and compared to a waiting-list (WL) condition. Participants will be assessed before and after the H.O.M.E. intervention/WL and at the 3- and 6-month follow-ups in the levels of the displayed dysfunctional behavior, the three transdiagnostic factors, and stress. Changes in dysfunctional behaviors, transdiagnostic factors, and stress in each population VR group and differences in such improvements between each population of the VR and WL groups will be evaluated using mixed-model repeated measure analyses of variance. It is expected that, after the H.O.M.E. intervention and at follow-ups, participants will display improvements in physical and psychological health compared to controls. The H.O.M.E. protocol is expected to result in a cost-effective option to tackle cognitive–behavioral factors shared among several psychopathologies and dysfunctional behaviors.

## 1. Introduction

The term “Virtual Reality” (VR) refers to an array of technologies that allow individuals to experience and interact with computer-generated three-dimensional environments and objects through a head-mounted display [1]. The high levels of immersivity and realism offered by VR make individuals experience a sense of “emotional presence”, which is comparable to reality in inducing emotional responses [2,3]. Because of this, VR has been used in clinical psychological contexts as an instrument to offer patients systematic and controlled exposure therapy without the complications of in vivo exposure [4]. VR is also capable of improving existing cognitive-behavioral treatments (CBT) and prevention protocols for several psychiatric disorders, especially in patients with anxiety, psychosis, substance-related, and eating disorders (EDs) [5,6]. Although VR software and protocols have been developed mainly following a disorder-specific approach [6,7], VR programs capable of being administered transdiagnostically across several psychiatric diagnoses have also been recently designed for the improvement in transdiagnostic aspects, particularly emotion regulation strategies [8].

According to the transdiagnostic approach, many psychological disorders and comorbid psychiatric diagnoses are maintained or caused by similar cognitive and/or behavioral processes [9,10,11], defined as transdiagnostic factors. While research has not reached a consensus regarding which transdiagnostic factors should be mainly implicated in the development of psychological disorders, the assumption that certain shared cognitive and behavioral processes maintain or lead to the onset of many psychological disorders has been supported in the literature [11,12]. Within the third wave of the cognitive behavioral theory of mental disorders [13], clinical studies showed that several behaviors that might be detrimental to individuals’ health (such as heavy drinking, heavy smoking, or dysfunctional eating behaviors) are related to high levels of psychological inflexibility [14,15,16], emotion dysregulation [17,18,19], and experiential avoidance [20,21]. These transdiagnostic factors have also been found to correlate to higher stress levels [22,23,24]. Indeed, some transdiagnostic VR software protocols have been developed for the improvement in emotion regulation (ER) strategies [8] and were found capable of reducing unhealthy behaviors and lifestyles (e.g., heavy smoking, heavy drinking, or dysfunctional eating behaviors) in the general population [5,6,25,26,27,28,29,30]. However, no transdiagnostic VR software or intervention has been designed yet to tackle more than one unhealthy behavior within the same software. Moreover, the beneficial effects of VR-based interventions, including the improvement in experiential avoidance and psychological flexibility, have not been proven yet. In particular, no VR software has been designed to concurrently tackle these third-wave cognitive–behavioral transdiagnostic factors and multiple unhealthy behaviors and lifestyles.

To fill this gap in the literature, researchers and clinicians (clinical psychologists and psychotherapists [name], [name], and [name] and psychiatrist and psychotherapist [name]) from the Department of Psychology of the University of Bologna designed a transdiagnostic VR software and intervention protocol (H.O.M.E.—How to Observe and Modify Emotions) to improve emotion regulation, experiential avoidance, and psychological flexibility in order to make them suitable for several clinical and non-clinical populations. The H.O.M.E. intervention was designed to be a six-session intervention protocol focusing on the assessment of emotions elicited by trigger cues present in the virtual environment (e.g., comfort foods, cigarettes, alcohol, etc.) and the tackling of these emotions through CBT-based exercises to enhance the aforementioned transdiagnostic factors.

In particular, this study presents the research protocol for a randomized controlled trial designed to evaluate the effects of H.O.M.E. VR-based intervention in ameliorating the frequency and severity of unhealthy behaviors (i.e., heavy smoking, heavy drinking, and dysfunctional eating behaviors) and three transdiagnostic factors (emotion regulation, experiential avoidance, and psychological flexibility) levels in individuals of the general population that are considered at risk for nicotine dependence, alcohol abuse, or eating disorders. These experimental groups will be compared to a waiting-list condition consisting of a 6-week duration with weekly phone check-ups. The hypotheses are that H.O.M.E. will prove to be effective in reducing the frequency and severity of unhealthy behaviors as well as improving the transdiagnostic factors, even when compared to the waiting-list condition.

## 2. Materials and Methods

### 2.1. Design

The present study is a randomized controlled trial (RCT) protocol involving individuals from the general population presenting three different types of unhealthy lifestyles and behaviors (i.e., people who engage in heavy smoking, heavy drinking, or report dysfunctional eating behaviors), each one randomized into two treatment arms: an intervention group that will receive the H.O.M.E. VR-based intervention and a control group assigned to a waiting-list condition. The RCT follows the guidelines of the Standard Protocol Items: Recommendations for Interventional Trials (SPIRIT) [31] and the Consolidated Standards of Reporting Trials (CONSORT) [32] and was approved by the ethical committee of the Department of Psychology, University of Bologna (Protocol N. 314877, 14 December 2021).

### 2.2. Participants and Sample Size

Individuals from the general population (age range: 18–60 years) exhibiting unhealthy lifestyles and behaviors (i.e., heavy smoking, heavy drinking, and dysfunctional eating behaviors) and are at risk for nicotine dependence, alcohol abuse, or eating disorders will be recruited via social media by filling an online battery of self-report psychometric questionnaires (administered via the Qualtrics online platform).

The inclusion criteria will include the following: (a) being between 18 and 60 years of age; (b) having no prior diagnosis according to the DSM-5-TR [33] diagnostic criteria; (c) displaying one of the unhealthy lifestyles and behaviors mentioned above according to the relative screening questionnaires (see Screening measures below).

The exclusion criteria will include the following: (a) lack of capacity to consent for research; (b) current or former diagnosis of psychiatric disorders according to the DSM-5-TR diagnostic criteria; (c) using medical devices (e.g., pacemaker and hearing aids) or having a medical condition (e.g., vertigo and vision impairments) that may interfere with VR technologies; (d) having concurrent physical health conditions that might better explain the presence of these unhealthy behaviors.

Participants will be enrolled until reaching a number of around 64 individuals for each of these three separate samples: (1) individuals who engage in heavy smoking, (2) individuals who engage in heavy drinking, and (3) individuals who report dysfunctional eating behaviors. The sample size was calculated using G*Power [34] and considering our main statistical analyses (repeated measure ANOVAs with a medium effect size of 0.25, power of 0.80, two groups, and four time measurements), with an addition of an estimated 30% drop-out rate.

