### 2.3. Procedure

In the screening phase, participants will fill in online (via the Qualtrics platform) a non-psychometric self-report questionnaire and several self-report psychometric screening questionnaires for the detection of three unhealthy lifestyles and behaviors: heavy smoking, heavy drinking, and dysfunctional eating behaviors (see Screening measures). Individuals interested in taking part in the research will be informed of the aims and characteristics of the study. If they agree to participate, they will be asked to sign an informed consent online on Qualtrics. Participants who provide written informed consent will be screened, and if suitable to participate, will be subsequently contacted via e-mail or smartphone within 7 days and invited to take part in the experimental phase of the study.

In the experimental phase, participants in each of the three samples will be randomized to the intervention (VR) or control (waiting-list) condition following a “block randomization” method [35]. Before randomization, participants will undergo a brief clinical interview based on the DSM-5-TR criteria conducted by a charted clinical psychologist researcher to exclude the presence of DSM-5-TR psychiatric disorder diagnoses. Participants in the VR group will undergo six 30 min sessions of the VR-based intervention administered using the software H.O.M.E. in the presence of a clinical psychologist (the intervention protocol is illustrated below). Controls (waiting-list group) will not receive any intervention during the study, but they will receive minimal attention from researchers through phone check-up sessions to monitor their symptoms and general well-being. They will also be offered to receive the VR-based intervention after concluding the study.

To test whether changes will be maintained over time, both groups will be re-contacted for follow-ups after 3 and 6 months.

Immediately before the first session of the intervention phase (T0), at the conclusion of the intervention phase (T1), and at the 3 (T2) and 6-month follow-ups (T3), participants of all groups will be asked to complete a series of psychometric self-report questionnaires online (using the Qualtrics platform) (see Outcome measures).

More details about the allocation of participants and the RCT design are shown in Figure 1.

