##### VR-Based Intervention Group

The proposed VR-based intervention will consist of six weekly sessions of approximately 30–50 min. The intervention will take place at the VR laboratory of the Department of Psychology of the University of Bologna. The intervention protocol will be delivered by a clinical psychologist (author [name]).

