The six VR-based intervention sessions will have different aims and will be divided as follows:(1)Session 1 will focus on gathering information about the participants and instructing them on the use of virtual reality interfaces. During this session, the participants will have the time to familiarize themselves with the H.O.M.E. software VR environment, and the clinician will verify if any motion sickness symptoms or difficulties in using the VR device are reported by participants.(2)Session 2 will focus on the interaction with the objects in the virtual HOME environment that are the most relevant for the participant (i.e., foods, drinks, electronic devices, cigarettes, etc.). During this session, the participant will be asked to attribute to each relevant object the emotions they associate with it and its intensity (this will be performed via the assessment phase of the H.O.M.E. software). CBT-based homework (in particular, filling in an Antecedents, Behavior, Consequences-ABC worksheet throughout the subsequent week) will be given to the participant at the end of the session.(3)Session 3 will focus on recreating critical situations that the patient wrote in the ABC worksheet in the H.O.M.E. software and further discussing the relevant objects and elicited emotions.(4)Session 4 will focus on illustrating to the participants all the psychological/behavioral resources present in the “box of resources”. The participants will then be asked (with help from the clinical psychologist, if needed) to select the resource they think will be the most beneficial to overcome the distressing emotions previously attributed to the critical objects (this is performed using the intervention phase of the H.O.M.E. software). The clinician will also discuss with participants how to use this resource in the real world, and the participants will be asked to apply it in everyday life during the following week as homework.(5)Session 5 will focus on discussing the difficulties participants might have experienced when trying to use the resource in their everyday life, and if needed, additional exercises will be conducted in the virtual environment to better use the resource. Alternatively, the participant might be asked to select an additional resource they would like to explore.(6)Session 6 will focus on re-evaluating the objects the participant previously selected as critical and evaluated in Session 2 to assess possible changes in the intensity and type of emotions attributed to them after using the psychological resources to deal with them in a real-life context.

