#### 2.5.1. Screening Measures

All participants who will provide written informed consent and meet the criteria to be included in the experimental part of the study will be asked to fill in the following questionnaires:−A non-psychometric self-report questionnaire to collect socio-demographic (age, marital status, educational level, and occupational status) and clinical data (body mass index (BMI), former DSM-5-TR diagnosis, and clinical conditions and/or use of medical devices interfering with VR) and to investigate the participants’ familiarity with the use of a computer or technological devices (i.e., computer and videogames) in their everyday life.−The Alcohol Use Disorders Identification Test (AUDIT) [38] is a 10-item psychometric screening tool developed by the World Health Organization (WHO) to assess alcohol consumption, drinking behaviors, and alcohol-related problems. AUDIT scores higher than five indicate a potentially harmful pattern of drinking, with a sensitivity of 0.84 and a specificity of 0.90 in the Italian population [39].−The Fagerström Test for Nicotine Dependence (FTND) [40,41] is a 6-item self-report psychometric instrument for assessing the intensity of physical addiction to nicotine in terms of the quantity of cigarette consumption, compulsion to use, and dependence. Scores between three and four at the FTND indicate a low-to-moderate dependence, scores between five and seven indicate a moderate dependence, and scores higher than eight indicate a high dependence. The Italian version of the FTND showed low internal consistency reliability, with a Cronbach’s alpha of 0.55 in the combined sample (=0.59 among men and =0.50 among women) [41].−The Eating Disorders Examination Questionnaire (EDE-Q 6.0) [42,43] is a 28-item psychometric self-report questionnaire to evaluate their levels of ED psychopathology. The EDE-Q focuses on the past 28 days and produces a global score as well as four subscales: Eating Concern, Shape Concern, Weight Concern, and Restraint. The EDE-Q also includes items measuring the frequency of core ED behaviors, such as binge eating and compensatory behaviors. Higher scores are indicative of higher eating pathology, and scores between 1.56 and 3.91 are found to be associated with ED risk in the GP [44]. The EDE-Q demonstrated satisfactory concurrent validity [42,43] and acceptable internal consistency (Cronbach’s α ranging from 0.70 to 0.83 for the subscale and ≥0.90 for the global score) [45].

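### Entry criteria do not require availability for the six weekly laboratory sessions, and T0 is tied to the first session, so VR participants who never start may have no baseline

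*Protocol article*

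**What the plan says.** **Who may enter.** Section 2.2 of the protocol article lists conditions on age, absence of psychiatric diagnosis, a positive behavioural screen, capacity to consent and absence of an explanatory physical condition. One criterion concerns VR: it excludes people "using medical devices (e.g., pacemaker and hearing aids) or having a medical condition (e.g., vertigo and vision impairments) that may interfere with VR technologies". Section 2.5.1 shows that this is asked at screening, where the self-report form covers "clinical conditions and/or use of medical devices interfering with VR". No criterion concerns availability or travel, although candidates "will be recruited via social media by filling an online battery of self-report psychometric questionnaires".

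**What each arm must do.** For the VR arm, section 2.4.1 sets six weekly sessions and states: "The intervention will take place at the VR laboratory of the Department of Psychology of the University of Bologna". Section 2.4.2 gives controls phone check-ups only. All outcome questionnaires are completed online in both arms (section 2.3).

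**What happens before allocation.** Section 2.3 describes a clinical interview before randomisation. Its only stated purpose is to rule out psychiatric diagnoses.

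**When baseline is taken.** Section 2.3 fixes the first two assessments as follows: "Immediately before the first session of the intervention phase (T0), at the conclusion of the intervention phase (T1"). Sections 2.6 and 2.3 together make T0 part of every comparison between arms after baseline.

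**The concern.** Two choices combine. First, people who cannot come weekly to one laboratory can be randomised, and the difficulty shows only in those allocated to VR. A control with the same constraint can supply T0 to T3 from home. Second, baseline is placed after allocation and defined by an event that a VR non-starter never reaches.

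If such people drop out of the analysis, they leave the VR mean while their counterparts stay in the control mean. The arms then differ for a reason other than treatment, and a larger sample does not remove the difference. This works against section 2.6's stated reason for intention-to-treat, which is to keep the comparison as randomised.

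**Working it through.** **1. Which planned models need T0 (section 2.6)**
- Repeated-measures ANOVAs: T0 is one of four levels of the time factor.
- Repeated-measures MANOVAs: the same, with five dependent variables.
- MANCOVAs at T1, T2 and T3: T0 scores are covariates.

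Someone without T0 therefore has no complete record for any of them.

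**2. Which scores exist before randomisation (sections 2.5.1 and 2.5.2)**
- Collected at screening: AUDIT, FTND, EDE-Q.
- First collected at T0: DERS-16, AAQ-II, MPFI-EA, DASS-21.

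Of the five dependent variables in each sample, one has a pre-randomisation score and four do not.

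**3. Who is at risk of having no T0**
- VR participants who never attend: at risk, because T0 is tied to the first session.
- VR participants who stop during Session 1: not at risk, because T0 comes before that session.
- Controls: no session is needed, so T0 can be completed at home.

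**4. The plan's sample size, for scale**
Inputs from section 2.2: f = 0.25, power 0.80, two groups, four times, 30% drop-out, about 64 per sample. Not stated, so assumed: alpha 0.05, sphericity, correlation ρ between measures, 1:1 allocation.

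For the group-by-time interaction, λ = f² × N × 4/(1 − ρ), with 3 and 3(N − 2) degrees of freedom. With ρ = 0 and N = 45, λ = 0.0625 × 45 × 4 = 11.25 and power is 0.8005. Then 45/0.70 = 64.3, which reproduces the 64. With ρ = 0.5 the same formula gives 24, or 35 after drop-out. The point does not rest on this figure.

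**5. Effect of uneven loss on power**
The planned loss is 0.30 × 64 = 19.2, leaving 44.8. For arm sizes a and b, the effective N is 4ab/(a + b).
- Even loss, 22.4 and 22.4: effective N 44.8; power 0.80 (ρ = 0), 0.98 (ρ = 0.5).
- 45% of VR and 15% of controls, 17.6 and 27.2: effective N 42.7; power 0.78 and 0.98.
- All loss in VR, 12.8 and 32: effective N 36.6; power 0.70 and 0.96.

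Power is the smaller issue.

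**6. Bias if non-starters are lost**
If a share p of the VR arm is lost and differs from the rest by s SD, the VR mean shifts by p × s. The documents give neither quantity. Assumed range: p = 0.05 to 0.20 (1.6 to 6.4 of 32) and s = 0.3 to 0.5.
- Low: 0.05 × 0.3 = 0.015 SD.
- High: 0.20 × 0.5 = 0.10 SD.

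**7. Dilution if everyone is followed**
This illustration uses a simpler test than the planned ANOVA: a two-sample t-test, two-sided 5%, 32 per arm with no loss, and no benefit in non-starters. A difference of d = 0.711 has 80% power. With 5, 10 or 20% untreated, d falls to about 0.68, 0.64 or 0.57, and power to 75.9, 71.3 or 61.1%.

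**The case against.** A reader might infer three stronger claims, and the documents support none of them.

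- **That tolerating VR is not an entry condition.** The VR-related exclusion names vertigo and vision impairment, and the screening form asks about it before allocation in both arms. In Session 1 "the clinician will verify if any motion sickness symptoms or difficulties in using the VR device are reported by participants", but nothing says that anyone is excluded or withdrawn as a result.
- **That never-starters necessarily have no T0.** T0 is an online questionnaire asked of all groups and could be completed before a missed appointment. Controls have a T0 without any session, so the wording can be read as the start of the six-week phase.
- **That leaving the sessions means leaving the analysis, so that intention-to-treat fails.** T1 to T3 are online and need no travel, and intention-to-treat is declared for all analyses. Dilution is what that approach accepts, and section 2.6 itself calls the resulting estimate conservative. Handling of missing data may be set in a fuller document and is not counted here.

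The other side can also point to self-selection before randomisation, since section 2.3 says: "Individuals interested in taking part in the research will be informed of the aims and characteristics of the study". Consent material and the flow chart are not shown, and either may mention attendance. The 64 already contains a 30% allowance for drop-out.

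These arguments limit the point but do not remove it. Being informed is not the same as being confirmed available. A pooled drop-out allowance covers numbers, not imbalance between arms. The T0 rule as written is still tied to a session that some of the VR arm may never reach.

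**Conclusion.** The point holds in limited form. Availability for the sessions is not among the listed criteria, the burden falls on one arm, and T0 follows randomisation and is worded around the first session. VR participants who never start are at risk of an absent baseline, most clearly on the four scales not collected at screening.

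The size cannot be determined from the documents. The bias range of 0.015 to 0.10 SD rests wholly on the assumed 5–20% loss and 0.3–0.5 SD difference. If everyone is followed up online, there is dilution and no bias from this source. It is worth changing because the remedy alters who is randomised and when baseline is taken, at little cost.

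**What to change.** 1. In section 2.2, add an inclusion criterion: able and willing to attend six weekly laboratory sessions if allocated to VR. Confirm it for every candidate at the existing pre-randomisation interview.
2. In section 2.3, collect the online T0 questionnaires from everyone after that interview and before allocation. Failing that, use a fixed date common to both arms. Send the T1–T3 links on the same schedule to everyone randomised, whether or not they attend sessions.

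The second change matters most for T0; the first alone leaves its timing unchanged. An extra motion-sickness item at screening would add little to the existing VR exclusion.

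Cost: one criterion, a few sentences, a slightly narrower population (people who can reach the laboratory) and a few more screen failures.
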